## 1. Introduction

### 1.1 Lay summary

Probe-to-bone test (PTB) is a simple bedside clinical test to aid in the diagnosis of diabetic foot osteomyelitis (OM). While it has been shown to be useful (especially in a high-risk cohort), diagnosis of OM is supported by additional tests such as X-rays and blood tests for markers of infection. The gold standard test for diagnosing OM is a bone biopsy, which is often not routinely performed due to the invasiveness of the procedure and the difficulty with accessing clinicians trained in performing this. Patients with diabetic foot ulcers and positive PTB tests are often treated for OM with prolonged courses of antibiotics despite normal X-rays and/or normal biomarkers of infection.

This study aims to evaluate the safety and feasibility of treating patients with diabetic foot ulcers and positive PTB test with shorter courses of antibiotic therapy in a low-risk setting.

### 1.2 Introduction

Diagnosing diabetic foot OM remains of paramount importance, given progression often results in amputation. Biopsy of bone tissue for culture and histology remains the gold standard for diagnosis of OM. Due to the invasive nature and impracticality of this test in most patients, International Working group of Diabetic Foot (IWGDF) guidelines recommend use of probe-to-bone (PTB) test, plain X-rays and serum biomarkers of inflammation as initial tests to make the diagnosis.

Probe-to-bone test was first proposed in 1995 by Grayson and colleagues as an efficient bedside technique for diagnosing diabetic foot OM. This technique involves inserting a sterile blunt metal probe into a diabetic foot ulcer (DFU) to assess if bone is palpable. They noted that PTB had a high positive predictive value in a hospitalized cohort in diagnosing

OM. Subsequent studies have demonstrated high negative predictive value but lower positive predictive value in different populations. Specifically, the validity of positive PTB has been questioned in low-risk outpatient settings, where lower prevalence of OM in the population resulted in lower positive predictive value of positive PTB.

The International Working Group for Diabetic Foot (IWGDF) guidelines recommend using a combination of PTB, plain X-rays and serum biomarkers (e.g. ESR, CRP, procalcitonin) to diagnose OM in patients with DFUs. Plain X-rays have been shown to lack sensitivity in acute OM, but serial X-rays taken 2 to 6 weeks later have been shown to increase sensitivity. Other concurrent diagnoses such as Charcot arthropathy can mimic the changes of OM on plain X-ray and are not infrequently present in this population. Serum biomarkers of inflammation/infection are also routinely conducted in these patients with elevated ESR, CRP or procalcitonin to be useful in establishing the diagnosis of OM. However, no single biomarker or combination of biomarkers has been shown to have a high sensitivity in diagnosing OM.

While previous studies have attempted to validate the PTB test as a diagnostic tool, the optimal antibiotic therapy in these patients has not been previously assessed.

This study is a multi-site, pilot, feasibility and safety randomized clinical trial comparing short course antibiotic therapy to long course in patients with DFU that has positive PTB without X-ray findings of OM.

## 2. Study objectives

### 2.1 Hypothesis

In patients who have a diabetic foot ulcer with positive PTB test without X-ray changes of osteomyelitis, it is feasible and safe to recruit patients to a randomized controlled trial.

### 2.2 Study aims

To evaluate the feasibility and safety of short course of antibiotic therapy in patients with positive PTB test without initial X-ray changes of osteomyelitis.

### 2.3 Outcomes

#### **Primary Outcome measures**

The primary endpoint will be feasibility and safety of the trial.

#### Feasibility outcomes

Feasibility outcomes assessed will include:

- Eligibility to recruitment ratio
- Retention rate
- Adherence to protocol
- Cross-over from intervention to control group

#### Safety outcomes

- SAEs, including all-cause mortality
- Antibiotic-associated adverse event
- Clostridioides difficile* associated diarrhoea
- Number of hospital readmissions during the follow-up period related to treatment of diabetic foot infection or complications arising

## Secondary outcome measures

### Exploratory clinical outcomes

- Recurrence of infection at same or contiguous site, diagnosed clinically or radiologically requiring administration of multiple (>1) doses of antibiotic therapy within the follow-up period
- Recurrence or persistence of infection at same or contiguous site requiring surgical debridement/amputation within the follow-up period
- Persistence of infection at same site requiring continuation of antibiotics beyond the planned duration
- Development of new X-ray changes of osteomyelitis at day 14 and day 42 visit

## 3. Study design

### 3.1 Study type, design & schedule

This is a pilot, feasibility and safety, randomized controlled trial to be conducted in patients managed by the High Risk Foot Service at multiple sites in Melbourne, Australia.

Patients with diabetic foot ulcers with positive probe-to-bone test without radiological evidence of OM on initial plain X-rays will be identified by investigators and assessed for eligibility. We aim to recruit 120 participants and allocate them in a 1:1 ratio to the intervention group (2 weeks antibiotic therapy) and the control group (6 weeks antibiotic therapy).

Recruitment is planned to occur over an 18 month period from March 2024 to September 2025.

#### 3.1.1 Teletrial

This study will run as a teletrial with Austin Health acting as a primary site for regional satellite site (Bendigo Health), as per guidance from the National Standard Operating Procedures for Clinical Trials, including Teletrials, in Australia. A teletrial uses telehealth technology to communicate between the primary site and the satellite site to enable delivery of certain aspects of the clinical trial in a convenient way for patients living in regional, rural or remote locations. The principal investigator ([name]) will supervise associate investigators to conduct this trial at a satellite site (Bendigo Health). The principal investigator will remain responsible for the trial.

A detailed supervision plan, in addition to a delegation log will be developed and maintained for the satellite site.

### 3.2 Study population

Adult patient  $\geq 18$  years with diabetic foot ulcer and positive PTB test

### 3.3 Intervention

Patients will receive 2 weeks of antibiotic therapy from date of index X-ray demonstrating no radiological evidence of osteomyelitis.

### 3.4 Control

Patients will receive 6 weeks of antibiotic therapy from date of index X-ray demonstrating no radiological evidence of osteomyelitis.

### 3.5 Participant timeline

Total follow up period for participants will be 90 days from date of recruitment. In-person or Telephone/telehealth follow up will be conducted at 14 days (+/- 2 days), 42 days (+/- 2 days) and 90 days (+/- 5 days) from the date of recruitment.

Following recruitment, all patients will be randomized to either the intervention (2 weeks) or the control (6 weeks) group. Repeat X-ray and serum biomarkers will be performed at the 14 day and 45 day follow up timepoint.

[figure not shown]

**Figure 1: Study design overview**

### 3.6 Antibiotic choice

Antibiotic choice, including agent, dosing and route of administration, will be at the discretion of treating clinicians based on the results of any relevant microbiological culture and susceptibility results, such as wound swab cultures.

### 3.7 Baseline participant data

Participants will have the following baseline data collected (see Appendix 2):

- Age
- Sex
- Charlson Comorbidity Index
- HbA1c level within last 90 days

- e. Ankle-brachial pressure index and/or systolic toe pressure measurement
- f. Ulcer location
- g. Ulcer size
- h. Ulcer classification score (Wlfl)
- i. Antibiotic therapy prior to randomisation
- j. Serum biomarkers (total peripheral white cell count, serum C-reactive protein)
- k. Results of baseline wound swab for bacterial culture

### 3.8 Randomisation

Randomisation will be performed by permuted block design with a block size of 4 participants via REDCap and allocation sequence will be concealed until the time of randomisation. Allocation sequence will be created by an independent statistician.

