### 3.10 Follow up radiology assessments

Repeat X-rays will be performed at the day 14 and day 42 visit. If feasible at the site, study investigators will be blinded to the result of these X-rays and reporting of the X-rays will be done by an independent panel of radiologists. Results of these X-rays will not be released to study investigators until recruitment and follow up of patients is complete. Where blinded radiology assessments are not feasible, follow-up radiology will be performed in an unblinded manner.

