### 4.3 Exclusion criteria

- Systemic antimicrobial therapy for >7 days in the 30 days prior to initial enrollment
- Systemic signs of sepsis based on SIRS criteria
- Initial surgical therapy deemed more appropriate than medical management alone of diabetic foot infection
- Treating clinician deems no antibiotic therapy required
- Known pregnancy

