### 6. Statistical methods

#### 6.1 Sample size estimation and justification

This is a pilot trial, aiming to assess the feasibility and safety of short course therapy in diabetic foot ulcers with positive PTB and no X-ray changes of OM. This will also provide local estimates for power calculation in future trials.

We will recruit a total of 120 participants (60/group) as this will provide precise estimates of feasibility outcomes (with confidence interval of <20%). Such sample size will also provide a reliable estimate for future trials, as it has been shown that the gain in precision of binary outcome is smaller once each group reaches 60 participants.

Based on our local experience, we estimate approximately 3 patients per week present with positive PTB and normal X-rays. Assuming a 50% recruitment rate, this would result in 117 eligible patients in an 18 month period. Therefore the trial recruitment is likely to be completed within around 18 months.

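### The protocol discloses one fixed block size of 4 in a multi-site trial that is unblinded in practice, and does not say whether blocks run within site; either reading has a cost

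*Protocol*

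**What the plan says.** Section 3.8 of the Protocol is the whole account of randomisation: "Randomisation will be performed by permuted block design with a block size of 4 participants via REDCap". It adds that the "allocation sequence will be concealed until the time of randomisation" and "Allocation sequence will be created by an independent statistician". Section 3.1 says the trial will "allocate them in a 1:1 ratio to the intervention group" and the 6-week control group, and Section 6.1 plans 120 participants, 60 per group. No stratification factor is named, and nothing says whether the blocks belong to one central list or to a list at each site.

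Other sections matter here:

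- **Sites.** The synopsis lists five centres, one of them a satellite. Section 8 says patient-level data are not shared between sites. Section 3.1.1 has the principal investigator at the primary site supervise the satellite.
- **Blinding.** The words open-label do not appear. The arms differ in visible treatment length and no placebo is described. The only blinding described is for the adjudicators of serious adverse events (Section 5.1) and, where a site can manage it, for follow-up X-rays. Section 3.10 continues: "Where blinded radiology assessments are not feasible, follow-up radiology will be performed in an unblinded manner".
- **Entry.** Under Section 4.1 patients are approached once the probe-to-bone test is positive, and eligibility is settled after the X-ray and before randomisation. Two exclusions in Section 4.3 rest on judgement: "Treating clinician deems no antibiotic therapy required" and "Initial surgical therapy deemed more appropriate than medical management alone of diabetic foot infection".

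**The concern.** Concealing the list stops a recruiter from reading ahead. It does not stop deduction. Someone who knows that every block holds two of each arm, and has seen the earlier allocations in the list, can work out the last place in each block and sometimes the last two. A recruiter who expects the 2-week arm next could use one of the judgement-based exclusions for a patient thought too ill for it. That would bias the between-arm safety and clinical risk differences planned in Section 6.2, and would also shift the eligibility-to-recruitment ratio. Safety is part of the primary endpoint in Section 2.3.

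This needs the recruiter to see most of the list. If the list is shared by five centres, the exposure is different: nothing then balances the arms within a site. X-ray blinding may differ by site, so an unbalanced site would mix treatment arm with the way new X-ray changes are read. That outcome is one of the exploratory ones in Section 2.3.

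**Working it through.** **Inputs from the Protocol.** Block size 4 (Section 3.8), ratio 1:1 (Section 3.1), 120 participants with 60 per group (Section 6.1), five centres (synopsis).

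**Assumptions.** The Protocol gives no site sizes. Two cases are used: 24 per site (120/5), and average sizes of 42, 30, 24, 18 and 6.

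**The plan's own figure.** 120/4 = 30 complete blocks, and 30 × 2 = 60 per arm. The block size fits the planned 60/60 split.

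**Reading 1: one list per site, and the recruiter sees every earlier allocation in it.** There are 6 equally likely orders of AABB. The recruiter guesses the arm that is behind within the block and tosses a coin when the arms are level.

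| Place in block | Chance it is certain | Chance of a correct guess |
|---|---|---|
| 1 | 0 | 1/2 |
| 2 | 0 | 2/3 |
| 3 | 1/3 (first two alike) | 1/3 × 1 + 2/3 × 1/2 = 2/3 |
| 4 | 1 | 1 |

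- Certain: (0 + 0 + 1/3 + 1)/4 = 33.3%, or 40 of 120 if all blocks are complete.
- Guessed correctly: (1/2 + 2/3 + 2/3 + 1)/4 = 70.8%, or 85 of 120, against 60 by chance.
- The arms at a site can never differ by more than 2 patients.

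**Reading 2: one central list in blocks of 4, and the recruiter sees only own-site allocations.** Simulated with 120 patients spread at random over five sites, 6,000 runs.

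- Guessing the arm that is behind at the own site succeeds 51.5% of the time with equal sites and 51.8% with unequal sites.
- At a site averaging 24 patients the arms differ by about 3.5 on average, and by at least 6 (such as 15 v 9) with probability about 0.21.
- The probability of a difference of at least 6 depends on average site size: 0.29 at 42, 0.24 at 30, 0.16 at 18 and 0.02 at 6.
- At least one of the five sites differs by 6 or more with probability 0.64 (equal sites) or 0.58 (unequal sites). The overall split stays at 60/60.

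**Effect of varying the block size within site.** Simulated for a 24-patient list, 4,000 runs. The guesser sees the whole site list, knows the set of possible sizes and always makes the best guess.

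| Block sizes | Certain | Best guess correct |
|---|---|---|
| 4 only (exact) | 33.3% | 70.8% |
| 2, 4, 6 | 3.9% | 69.7% |
| 4, 6 | 5.9% | 68.7% |
| 4, 6, 8 | 2.4% | 67.2% |

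Varying the sizes removes nearly all certainty but lowers the guess rate by only 1 to 4 percentage points. Sizes 4, 6 and 8 do best on both counts.

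**The case against.** Several counter-arguments have force.

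- **The structure is not stated.** A reader might infer from the silence of Section 3.8 that the list is unstratified. The Protocol does not say so, and strata are often set out in a statistical analysis plan or in the REDCap set-up. The point therefore rests on what is stated, the disclosed fixed block, and takes each list structure in turn.
- **The two harms are alternatives.** A reader might take the 71% guess rate and the site imbalance together. They cannot both apply in full: the first needs per-site lists or sight of all allocations, and on a central list guessing is close to chance. One partial exception is an investigator who oversees more than one site, as in the teletrial arrangement of Section 3.1.1, and so sees more of a central list.
- **Antibiotic choice is not tied to site.** A reader might add it as a further site effect. Section 3.6 leaves it to the treating clinician, guided by cultures, and says nothing of site. Only X-ray blinding is described as depending on site.
- **There are safeguards.** An independent statistician makes the sequence, REDCap delivers it, and a radiologist's report decides a main entry criterion. Section 4.1 logs all adults whose ulcers probe to bone. Section 3.11 audits patients excluded because the clinician preferred no antibiotics, so steering by that route would leave a trace. Adjudicators of serious adverse events are blinded. These limit the harm and help to detect it, but none of them stops deduction from a known block size.
- **This is a pilot.** Feasibility outcomes are pooled percentages, the clinical outcomes are labelled exploratory, and the Protocol plans estimates with intervals. This stands and limits the weight of the point.

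**Conclusion.** The point holds in a limited form. One small block size is fixed and printed in a document that recruiters read, in a trial that is unblinded in practice, and the list structure is left open.

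With per-site lists, 33% of allocations are certain and 71% can be guessed. These two figures are exact for a recruiter who tracks every allocation. With a central list, guessing is near chance at about 52%, and the cost is imbalance within sites: roughly a one-in-five chance of a difference of 6 or more at a site averaging 24 patients. Those figures depend on assumed site sizes.

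What is exposed is the between-arm safety and clinical risk differences under the first reading, and mainly one exploratory X-ray outcome under the second. Pooled feasibility percentages are little affected. Nothing in the Protocol shows that selection will occur; it shows only that the design leaves room for it. The change is a sensible, inexpensive improvement and does not bear on whether the trial can go ahead.

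**What to change.** 1. Have the independent statistician generate a REDCap list stratified by site, with block sizes varying at random, preferably 4, 6 and 8 rather than 2, 4 and 6. State whether the satellite is its own stratum.
2. In Section 3.8, say that randomisation is 1:1 in permuted blocks of varying size, stratified by site. Take the sizes out of the Protocol and keep them in a restricted document.
3. Present the between-arm risk differences stratified by site, for example by Mantel-Haenszel weighting.
4. Section 3.1 planned recruitment from March 2024. If enrolment has begun, apply the change to the unused part of the list, record the date, and report the structure used before it. Item 3 can be done in any case.

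**Gain.** Certain allocations fall from 33% to about 2%. Best-guess success falls only from 71% to about 67%, so the fix removes certainty more than guessability.

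**Cost.** One regenerated allocation table and a short amendment. Unfinished blocks may leave an overall imbalance of a few patients; the largest possible difference at a site rises from 2 with blocks of 4 to 4 with a block of 8. If the present list is central, own-site guessing becomes easier than now (about 52% to about 67%) in exchange for balance within sites. The sponsor should make that trade knowingly.

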### 3.9 Follow up assessment data

Follow up will be at Day 14 ( $\pm$  2 days), day 42 ( $\pm$  2 days) and day 90 ( $\pm$  5 days) from date of recruitment. Data collected at these assessments will include:

- Attendance at follow up
- Mode of follow up assessment (i.e. in-person, telehealth (video) or telephone consult)
- Medication-related adverse events (see Appendix 3)
- Medication adherence assessment (see Appendix 4)
- Ulcer size
- Wlfl score
- Serum biomarkers (total peripheral white cell count, serum C-reactive protein)
- Changes to antibiotic therapy

### 3.10 Follow up radiology assessments

Repeat X-rays will be performed at the day 14 and day 42 visit. If feasible at the site, study investigators will be blinded to the result of these X-rays and reporting of the X-rays will be done by an independent panel of radiologists. Results of these X-rays will not be released to study investigators until recruitment and follow up of patients is complete. Where blinded radiology assessments are not feasible, follow-up radiology will be performed in an unblinded manner.

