### 5. Participant Safety and Withdrawals

#### 5.1 Risk Management and Safety

Given this is a pilot feasibility study with a relatively low number of planned participants, a data monitoring committee will not be established. Serious adverse events will be referred to two independent clinicians blinded to the intervention with experience in infectious disease and diabetic foot infections for adjudication.

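### At masked sites the day 14 and day 42 films are withheld from study investigators past each participant's day 90, and the protocol gives a reading of new osteomyelitis no route to anyone responsible for the participant

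*Protocol*

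**What the plan says.** Section 3.10 of the Protocol schedules repeat X-rays at the day 14 and day 42 visits and sets up two regimes.

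- Masked sites: "If feasible at the site, study investigators will be blinded to the result of these X-rays". The films go to an independent radiology panel for reading. The release rule is: "Results of these X-rays will not be released to study investigators until recruitment and follow up of patients is complete".
- Other sites: "Where blinded radiology assessments are not feasible, follow-up radiology will be performed in an unblinded manner".

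The films feed a secondary, exploratory outcome in section 2.3: "Development of new X-ray changes of osteomyelitis at day 14 and day 42 visit".

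Section 1.2 gives the background. It states "Diagnosing diabetic foot OM remains of paramount importance, given progression often results in amputation". It then notes that plain films lack sensitivity in acute disease, but that "serial X-rays taken 2 to 6 weeks later have been shown to increase sensitivity".

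On oversight, section 5.1 says "a data monitoring committee will not be established" and refers serious adverse events, and nothing else, to two independent clinicians. The glossary ties a serious adverse event to death, threat to life, hospital admission or a longer stay, or lasting or significant disability. Section 2.3 makes safety part of the primary endpoint.

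**The concern.** Days 14 and 42 are weeks 2 and 6, the two ends of the interval in which section 1.2 says a repeat film adds sensitivity. The day 14 film also falls at about the time the 2-week course ends. At a masked site the trial takes these more informative films and then withholds the results from its investigators. Changes of osteomyelitis on the baseline film make a patient ineligible (sections 4.1 and 4.2), yet the same finding two weeks later reaches no study investigator while that participant is being followed.

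Masking an outcome reading is ordinary good practice. The difficulty is that section 3.10 does it without saying what happens to a positive reading in the meantime. The panel has no stated reporting time, no duty to tell anyone and no named recipient, and there is no rule for lifting the mask. What is at stake is evidence of new bone infection, in a trial whose aim is to judge whether a shorter course is safe.

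**Working it through.** **Inputs**

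- Follow-up of 90 days per participant, with visits at 14 ± 2, 42 ± 2 and 90 ± 5 days from recruitment (section 3.5).
- Recruitment over 18 months, March 2024 to September 2025 (section 3.1).
- Release only when recruitment and follow-up are both complete (section 3.10).
- Assumed, because the protocol gives months only: first participant on 1 March 2024 and last on 1 September 2025, which is 549 days. Alternatives tried: 31 March 2024 and 30 September 2025.

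**The plan's own figure.** The accrual figure behind the 18 months reproduces: 3 per week × 78 weeks × 0.50 = 117 (section 6.1).

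**Time from film to earliest release**

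Earliest release = recruitment date of the last participant + 90 days. Holding time = release date − film date.

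| Participant | Day 14 film | Day 42 film |
|---|---|---|
| Last recruited, nominal days | 90 − 14 = 76 | 90 − 42 = 48 |
| Last recruited, over visit windows | 85 − 16 = 69 to 95 − 12 = 83 | 85 − 44 = 41 to 95 − 40 = 55 |
| First recruited, assumed dates | 549 + 90 − 14 = 625 | 549 + 90 − 42 = 597 |
| First recruited, alternative dates and day 90 window | 590 to 659 | 562 to 631 |
| Mean under even accrual | 549/2 + 76 ≈ 350 | 549/2 + 48 ≈ 322 |

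The last participant recruited has the shortest hold, and even that one ends at day 90. So no masked film is released to investigators within a participant's own scheduled follow-up. One sentence in section 3.5 puts the second film at day 45 instead of day 42. On that reading the shortest nominal hold is 90 − 45 = 45 days, and the conclusion is the same.

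**Is there another route?**

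1. Monitoring committee: none (section 5.1).
2. Independent clinicians: they receive serious adverse events only (section 5.1).
3. Serious adverse event reporting: new changes on a film, without one of the listed consequences, do not meet the glossary definition.
4. The radiology panel: it reports the films, but section 3.10 names no recipient before the end of the trial.
5. Treating clinicians: they are mentioned apart from study investigators in sections 3.6 and 4.3, but section 3.10 neither bars them from the result nor provides for telling them.

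None of the five gives a positive reading a stated route.

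**The case against.** The strongest defence is that masking here is deliberate and useful. Nothing in the protocol masks the treatment arm from those giving care, and a visible film could prompt longer antibiotics, which is itself an exploratory outcome. Section 1.2 also warns that Charcot arthropathy can imitate osteomyelitis on plain X-ray and is fairly common in these patients, so a positive film is not proof of disease. This explains why a sponsor would mask. It does not explain why a positive reading should have no recipient, and section 3.10 already accepts unmasked films wherever masking is impractical.

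A second defence is that participants are not unobserved, and this stands. Ulcer size and WIfI score are recorded at follow-up visits (section 3.9), and blood tests are scheduled at days 14 and 42 (Appendix 1). Investigators are not masked to any of these. Recurrence can be diagnosed clinically, nothing forbids a film ordered for care, and deterioration leading to admission is a serious adverse event. The gap is therefore limited to new osteomyelitis that shows only on a masked study film.

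Two stronger readings are tempting, and the documents support neither.

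- A reader might infer that nobody at all can act on a positive film. Section 3.10 withholds results from study investigators only and is silent on treating clinicians. The roles may overlap in practice, but the protocol does not say so. What can be said is that no route is stated.
- A reader might want a count of participants with undisclosed osteomyelitis. The protocol gives neither the number of participants at masked sites, which could be anything from 0 to 120, nor the rate of new changes on film. Any count would also have to separate the arms, since controls are still on antibiotics at day 14, and to remove those whose clinical signs would prompt review anyway.

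The consent form is not among the material at hand, so what participants are told about withheld films is unknown. That lowers certainty a little but does not supply a route.

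**Conclusion.** The point holds in a limited form. At masked sites a stated rule keeps the day 14 and day 42 results from study investigators until after each participant's day 90. The shortest nominal holds are 76 and 48 days (69 to 83 and 41 to 55 over the visit windows). For the earliest recruits the day 14 film is held for about 590 to 659 days on the assumed calendar dates. For safety, though, what matters is that release always follows the participant's own follow-up, and this does not depend on those dates. No monitoring committee, adjudication step or event definition offers a positive reading another way to someone responsible for the participant.

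That fits poorly with the weight section 1.2 gives to diagnosis and to serial films, and with safety as part of the primary endpoint. Because clinical review and blood tests continue and the number affected cannot be derived, this is something the sponsor should fix, not a flaw that invalidates the design. It is a rule of conduct set in the protocol, so a separate statistical analysis plan would not be expected to cure it.

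**What to change.** Reconcile sections 1.2, 3.10 and 5.1 by protocol amendment:

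1. State how soon after each follow-up film the existing panel reports it, and lock that reading as the study outcome. Section 3.10 now fixes when results are released, not when they are read.
2. State who, outside outcome assessment, is told of a reading of new osteomyelitis, and when.
3. Keep outcome assessors masked to the films.
4. Log the date of each release.

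What care follows a release is for the sponsor and clinicians to decide and is not proposed here.

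The films and readers stay the same. The cost is an amendment, a turnaround time for the panel and a release log. There is also a statistical cost, which should be stated openly. Locking protects the reading already made but not what comes after it. Release of a day 14 reading may change treatment before the day 42 film, and so may affect that film and the exploratory outcomes on antibiotic continuation, recurrence and surgery. It would be wrong to describe the X-ray outcome as unaffected. Report these outcomes with released cases identified. The affected outcomes are exploratory, whereas safety is part of the primary endpoint, so the exchange is reasonable.
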